**Figure 1 F1:**
[figure not shown]
**Device used to realize reproducible radiographs at each session**. The patient is asked to bite into a piece of silicone, which enables us to put the film holder and so the radiograph in the same position at each session. 1a: piece of silicone. 1b: film holder. 1c: Radiograph.

**Figure 2 F2:**
[figure not shown]
**The reproducibility of the radiographs taken at each session allowing us to compare them**. 2a: Radiograph taken during the inclusion session. 2b: Radiograph taken at the 6th month session. 2c: radiograph taken at the 12th month session.

### Evaluation criteria

The assessment criteria are both clinical and radiographic(Table 2).

**Table 2 T2:** Data reported in the CRF

Visits Data	V1	V2	V3	V4	V5	V6	V7
**Sex**	X						

**Age**	X						

**Clinical criteria**							

**Pain**	X	X	X	X	X	X	X

**Mobility(I, II, III, IV)**	X	X	X	X	X	X	X

**Swelling**	X	X	X	X	X	X	X

**Sinus tract**	X	X	X	X	X	X	X

**Abcess**	X	X	X	X	X	X	X

**Percussion tenderness**	X	X	X	X	X	X	X

**Radiographic criteria**							

**Degree of immaturity: Nolla stages: 7, 8, 9**	X						

**Endodontic filling**	X						

**Root resorption**	X						

**Periodontal ligament enlargement**	X	X	X	X	X	X	X

**Presence of an apical barrier**	X				X	X	X

**Radioluscent image**	X	X	X	X	X	X	X

**PAI**	X	X	X	X	X	X	X

**Form of the apical barrier**					X	X	X

#### Assessment with the patient at each session

First, the evaluation is realized at each session by the investigators-operators, who assess the presence or absence of clinical symptoms such as pain, abnormal mobility, swelling, sinus tract, abcess and percussion tenderness. Radiographic exams allow the evaluation of the main success criterion, the presence or absence of a calcified apical barrier as well as the presence of a radioluscent image and the form and thickness of the apical barrier. These investigators can compare all the patient's radiographs.

All these data are immediately entered in the CRF.

#### Anonymous evaluation at the end of the study

Two independent investigators will study all the anonymized X-Rays. This assessment will be done without the investigators having any information about the treated patients, their treatment or the nature of the × rays(preoperative, postoperative, after 3, 6 or 12 months). If the conclusions of the two investigators diverge, a third one will settle the matter. These anonymous data will be sent to the UCR that will then remove the anonymity before sending the service statistics for analysis.

### Expected benefits

The dental root canal can be hermetically filled immediately after the MTA hardens thus reducing the number of sessions and the length of the treatment.

### Predictable risks

Many *in Vitro *and *In Vivo *studies on MTA biocompatibility have been realized [21,25,26,41]. Ribeiro et al.(2006)demonstrated in an in vivo study, the absence of harmful effects of MTA [42]. Souza et al.(2006)carried out a study about the toxicity of 6 dental biomaterials and proved MTA was the least harmful of all [43]. This protocol does not involve any risks of serious side-effects entailed by the treatment.

### Undesirable events

Any adverse event observed during the study or the follow-up has to be reported in the CRF. Some information including occurrence time, duration, severity and treatment of this undesirable event should be noted as well. The relationship between adverse event and the apexification treatment has to be assessed(biological and mechanical failure).

### Monitoring and inspection

Monitor should regularly visit the dental office to control the process of study and the CRF, check storage of investigational dental products and record of data.

### Legal and ethical considerations

This study has been promoted by AP-HP(Paris Public Hospital)and approved by the ethics committee(CPP Paris Ile de France IV)and other French institutions:

- CNIL: French data protection watchdog

- AFSSAPS: the French Medecine and healthcare products regulatory agency, equivalent of the Food and Drug Administration in the United States.

Informed consent form(ICF)has been reviewed and approved by the ethics committee before study. Information about the protocol should be given to children and their parents both orally and in writing in an easily understandable language. The ICF must be dated and signed by the child and the parents(or representatives), and 3 copies must be made to be kept by the participants, the investigators and the UCR(15 years).

All information about the participants must be kept confidential.

### Statistical analysis

All the analyses followed an intention-to-treat principle and will be conducted to compare the efficacy of MTA with CH to induce root-end closure in necrotic permanent immature incisors at 6 months. Secondary efficacy endpoints are apical radiolucencies and PeriApical Index(PAI = 1, 2: healthy or PAI = 3, 4, 5: pathological)

Primary endpoints, ie, proportions of patients with an apical barrier close at 6 months will be compared between treatment groups with the Fisher's exact test, such as with the secondary endpoints.

To handle missing data on the primary endpoint, several procedures will be used where the missing values will be either dropped-out or replaced according to 3 simple imputation methods as follows:

- Observed data: patients with missing values are dropped out.

- Worst-case analysis: missing values are considered as a failure(apical barrier not closed at 6 months)in MTA group and as a success in CH group.

- Best-case analysis: missing values are considered as a success(apical barrier closed at 6 months)in MTA group and as a failure in CH group.

- Last Observation Carried Forward(LOCF):previous diagnostic is used to replace missing values.

The assessment of concordance between the two independent investigators about the closure of apical barrier at baseline, months 3, months 6 and months 12 will be given with the Kappa coefficient and the 95% confidence interval.

Analyses will be performed by two statisticians of Biostatistics and Epidemiology unit of Cochin Hospital(Paris)using SAS 9.1(SAS Institute Inc, Cary, North Carolina); tests will be 2-sided, and 0.05 will be used as the threshold for statistical significance.

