## Methods/Study design

### Objectives

- The main objective of this study is to test the ability of MTA, used as a root-end filling material, to induce a hard calcific barrier to seal hermetically non vital immature anterior permanent teeth with open apices over a 6 month's period.

MTA is a filling material allowing the creation of an artificial apical barrier-the MTA apical plug-but it is not good enough. The advantage of MTA is to induce a very close formation of mineralized tissue which is going to coat gradually the entire apex adhering to the MTA and the root walls. The interest of MTA is not only to create an immediate apical sealing(mechanical barrier)to induce a successful healing but also to promote the root-end growth or apexification, and finally the "bio-integration" of the non-vital immature permanent tooth.

- Secondary objectives:

• To assess the presence or absence of periapical radioluciency indicating the emergence or persistence of an apical periodontitis

• To compare the time required to obtain the clinical healing and the disappearance of clinical symptoms with the two materials: MTA and Calcium Hydroxide, when symptoms such as pain, swelling, sinus tract, abscess or abnormal mobility are present at the beginning of the study.

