### Subjects

The studied sample is composed of 34 children and teenagers, aged from 6 to 18 years presenting a pulp necrosis of a permanent immature incisor. The root maturation is normally completed 3 or 4 years after the tooth eruption, that is to say around the age of 9 or 10 years as far as incisors are concerned. However some teenagers present teeth damaged by a trauma before their maturation was achieved. That is the reason why such patients are included in the study when those traumas were not or unsuccessfully dealt with. The number of patients needed for this study was calculated prior to investigation with the hypothesis of a higher successful apexification rate in the MTA group compared to the control CH group. The anticipated success rates at 6 months were 5% in the CH group and 50% in the MTA group; Given these hypotheses, it was necessary to include 15 patients in each group that is to say a total of 30 patients to have a 80% statistical power(with a α risk of 5%), to compare the proportion of apical closure at 6 months with a Chi-2 test(two sided). Taking into account an anticipated dropout of 5%, it was decided to include 34 patients. Sample size calculations were computed with nQuery Advisor^® ^6.01. For ethical reasons, the sample size was limited while remaining compatible with the ability to obtain a significant difference between the two materials. The case reports published in the literature show a periapical repair within the first 6 months whereas the apical bridging induced with calcium hydroxide is more often obtained after a period of 6 to 18 months. That is why we hypothesized that after a period of 6 months, at least half of the MTA cases would be a success for the main objective as opposed to a minimal percentage for the calcium hydroxide group.

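### PAI and radiolucency are compared by an unadjusted Fisher's test although both are recorded at baseline and the objective depends on baseline status: valid, but inefficient and unable to separate emergence from persistence

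*Protocol article*

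**What the plan says.** The Statistical analysis section names the endpoints, "Secondary efficacy endpoints are apical radiolucencies and PeriApical Index", and splits the index as "PAI = 1, 2: healthy or PAI = 3, 4, 5: pathological". The method is set in one clause: the primary proportions "will be compared between treatment groups with the Fisher's exact test, such as with the secondary endpoints". The section directs the analyses to 6 months and adds that "tests will be 2-sided, and 0.05 will be used as the threshold for statistical significance". It describes no covariate or stratification factor for these comparisons.

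Under Objectives, the radiographic secondary objective is the presence or absence of a periapical radiolucency, "indicating the emergence or persistence of an apical periodontitis".

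In Table 2 (radiographic criteria), the rows "Radioluscent image" and PAI are marked at all seven visits, V1 to V7. The baseline value and the full five-point score are therefore both collected. The Randomization section describes blocks of 4 at 1:1 and mentions no stratification.

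**The concern.** Emergence can occur only in a tooth without disease at baseline, and persistence only in a tooth that has it. The inclusion criteria do not require a periapical lesion, so a mix of both is to be expected. A pooled table of 6-month status has neither denominator: a pathological tooth at 6 months may be an old lesion that did not heal or a new one.

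The second issue is efficiency. With 17 teeth per arm, the planned test leaves out the baseline reading and, for PAI, the ordering within the two classes. It may therefore miss a real difference in periapical healing, or return an estimate that partly reflects who happened to have a lesion at entry.

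**Working it through.** **The plan's own figure.** The only sample-size calculation is for apical closure. "The anticipated success rates at 6 months were 5% in the CH group and 50% in the MTA group", with two-sided alpha 0.05, 80% power and a chi-square test. With pooled p = (0.05 + 0.50)/2 = 0.275:

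n = [1.96·√(2 × 0.275 × 0.725) + 0.842·√(0.05 × 0.95 + 0.50 × 0.50)]² / 0.45² = (1.238 + 0.459)² / 0.2025 = 14.2, so 15 per arm, as stated. Inflating for 5% dropout, 30/0.95 = 31.6, so 32; the plan takes 34, or 17 per arm. Nothing comparable is given for PAI or radiolucency, so everything below rests on stated assumptions.

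**Fisher's test against a baseline-adjusted five-point analysis.** Assumed model: baseline and 6-month PAI are five ordered categories of a bivariate normal variable; 17 per arm; shift 0.6 to 1.3 SD; correlation 0 to 0.7; 4,000 simulated trials per scenario.
- The ratio of power, Fisher on the dichotomy to rank ANCOVA with baseline PAI, runs from 0.27 to 0.79.
- Example: even categories, shift 1.0 SD, correlation 0.5 gives 0.50 against 0.82, and 0.50/0.82 = 0.61.

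**How much is the cut and how much is Fisher.** Assumed: even categories, common odds ratio 5, 17 per arm, no baseline used, 20,000 trials.

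| Test | Power |
|---|---|
| Fisher, two classes | 0.474 |
| Uncorrected chi-square, two classes | 0.622 |
| Wilcoxon, five categories | 0.704 |

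The total loss is 0.704 − 0.474 = 0.230. Of this, 0.622 − 0.474 = 0.148 is Fisher's conservatism (its actual size here is about 0.02) and 0.704 − 0.622 = 0.082 is the cut.

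**A case where the cut does no harm.** Assumed PAI 1 to 5 probabilities of 0.15, 0.15, 0.25, 0.25, 0.20 under calcium hydroxide and 0.15, 0.60, 0.05, 0.05, 0.15 under MTA, so that most movement crosses the 2/3 boundary. With 17 per arm, Fisher has 0.675 and the unadjusted Wilcoxon 0.405, a ratio of 1.67. Over the assumed cases of this kind, with 15 or 17 per arm, the ratio was 0.97 to 1.75.

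**Stratifying the binary comparison on baseline status.** In the latent model (17 per arm, shift 0.6 to 1.3 SD, correlation 0 to 0.6):

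| Analysis | Power over the scenarios |
|---|---|
| Pooled Fisher | 17–76% |
| Exact test stratified by baseline status | 21–81% |
| Rank ANCOVA, five points | 35–98% |

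Stratification gains about 2 to 10 percentage points. Type I error of the adjusted tests is about 5% or less.

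**Chance imbalance at baseline.** With 17 per arm, a gap of 20 points or more means at least 4 teeth, since 4/17 = 23.5% and 3/17 = 17.6%. Enumerating two independent binomials with assumed baseline disease of 50%, 60% and 70%, the probability is 0.229, 0.220 and 0.189.

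For illustration, let 12/17 and 8/17 be diseased at baseline, with no effect of material, emergence of 5% and persistence q. The expected difference in the pooled table is (4/17)(q − 0.05): 0.082 for q = 0.40 and 0.176 for q = 0.80.

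**The case against.** The healthy/pathological split is fixed in advance and easy to read. It matches an objective worded as presence or absence; a move from PAI 4 to 3 is still pathological by the plan's definition. PAI is a secondary endpoint, the trial was sized for closure and kept small for ethical reasons, and supporting ordinal analyses may stand in an analysis plan that is not shown. These points stand. They are why the dichotomy should be kept and why this is not an error in the endpoint definition.

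A reader might infer that the plan roughly halves the power for PAI. The documents do not support a single figure, because they give no PAI distribution, effect or baseline correlation. Halving lies inside the range for moderate effects; the loss is smaller for large ones and can reverse when the effect sits at the cut.

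A reader might also infer that baseline imbalance makes the test invalid or drives its result. It does not: chance imbalance is already part of the null distribution under randomisation, and Fisher's simulated type I error is 2.2–2.4%, below nominal. Imbalance affects the precision of the one estimate obtained, not the validity of the test.

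Finally, separate tests of persistence and emergence would have little power. In the latent model at a 0.9 SD shift, with 50–60% diseased at baseline, they reach 22–31% and 8–13%. That is a reason to report them descriptively only.

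What the objection does not remove is that the unadjusted test is a stated choice, that baseline data already collected go unused in it, and that the pooled table cannot separate the two events the objective names.

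**Conclusion.** The point holds as one of efficiency and of fit to the objective, not of validity. The planned Fisher tests are valid. Under assumed latent-shift models with 17 per arm (0.6 to 1.3 SD, correlation 0 to 0.7), Fisher on the PAI dichotomy keeps about 0.3 to 0.8 of the power of a baseline-adjusted five-point analysis. Part of the shortfall is Fisher's conservatism, and the ordinal advantage can disappear if the effect is concentrated at the 2/3 cut. Stratifying the binary test on baseline status brings a modest gain, about 2 to 10 points in the scenarios examined. The mismatch with the objective needs no assumption about power. The primary endpoint is not affected.

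**What to change.** - Keep the pre-specified healthy/pathological PAI endpoint and radiolucency. At 6 months, compare each between arms by an exact test stratified by its own baseline status at V1.
- Tabulate, by arm and without testing, persistence among teeth diseased at baseline and emergence among teeth healthy at baseline.
- Add, as a supporting analysis, a five-point PAI comparison at 6 months adjusted for baseline PAI: rank ANCOVA with a permutation p-value, since the usual p-value is approximate at this size, or proportional-odds regression.

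The cost is a change of analysis wording and slightly more analysis work. The strata will be small, and a stratum with teeth in only one arm adds nothing to the test. No new data are needed: the CRF holds the baseline values, and the masked reading described under Anonymous evaluation already includes the preoperative films.

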## List of abbreviations

AFSSAPS: Agence Française de Sécurité Sanitaire des aliments et produits de santé; AP-HP: Assistance Publique-Hôpitaux de Paris; CH: Calcium Hydroxide; CNIL: Commission Nationale Informatique et Liberté; CRF: Case Report Form; EDTA: Ethylenediaminetetraacetic acid; ICF: Informed Consent Form; MTA: Mineral Trioxide Aggregate; PAI: Periapical Index; UCR: Unity of Clinical Research
